### Assessments

#### Sociodemographic variables

Sociodemographic variables will be collected at baseline, including age, gender, ethnicity, education level, family history of mental illness, economic condition, and marital status.

#### Physical parameters

Physical parameters will be collected at baseline and immediately after 8 weeks intervention. The Ultrasonic Health Examination Scale made by Sonka Medical Co., limited (SK-X80/TCS-160D-w/h) will be used to measure the height (m) and body mass (kg). Body Mass Index (BMI) will be calculated by formula^2^: BMI = weight/height^2^.

#### Cardiorespiratory fitness

As maximum oxygen uptake (VO_2*max*_) is the gold standard of exercise physiology for evaluating cardiorespiratory fitness, Chest Step Test will be hold to assess VO_2*max*_ at baseline, with the recommendation of test manual (53).

#### Clinical variables

Individuals will be diagnosed by two psychiatrists according to DSM-5 diagnostic criteria. The Mini-International Neuropsychiatric Interview (MINI), a short structured diagnostic interview, will be used to confirm the diagnosis (54).

Depression symptoms will be measured by HMRD 17, which was designed by Hamilton in 1960 (55). The reliability of Chinese version of HMRD-17 is 0.88–0.99 and the validity is 0.92 (50). Some items are defined by increasing intensity, and others are defined by number of equal valued terms. According to Davis JM, the scores of HMRD 17 ≤ 7 indicate that individuals do not have depressive symptoms; the scores >7 and ≤17 indicate that individuals have minor or moderate depression; the score >24 indicate that individuals have major depression. Two trained psychiatrists will independently conduct the assessments. This is the most widely used clinical scale and contains 17 variables.

Depression symptoms will also be measured by the Self-Rating Depression Scale (SDS), which was designed in 1965 by Zung and recommended by the United States Department of Education, Health and Welfare in psychopharmacological research (56). SDS includes 20 items, of which 10 items are positive and 10 items are negative. The form will be directly filled by patients. The row score will be derived by adding up 20 items, with maximum possible score being 80. Index score is equal to the row score × 1.24, expressed as decimal. The standard score in China is 53 and the cutoff value of total row score is 41, which is similar to the results of a study in the USA (57).

Manic symptoms will be measured by the Young Manic Rating Scale (YMRS), which contains 11 items (58). YMRS was designed by Young in 1978, and is the most widely used manic scale worldwide. YRMS contained 11 items. Five choices are included in items 1–4, 7, 10, 11, ranging from scores 0–4, while the items 5, 6, 8, 9 have five choices scored in double points (score of 0, 2, 4, 6, 8). The score ranges from 0 to 40. When the total score ≥5 and ≤10, individuals have manic symptoms and when the score ≥22, individuals have severe manic symptoms. The reliability and validity of YRMS have been examined in a previous study.

#### Biological variables

Blood samples will be collected using EDTA anticoagulant tubes at baseline and after eight weeks of intervention, and stored at 4^°^C for less than 1 h before being sent to the laboratory at The First Affiliated Hospital of Chongqing Medical University. Plasma level of CRP will be measured by emulsion method with Roche Cobase 701. The levels of IL-6 and TNF-α will be measured by chemiluminescence with Siemens ZMM1000. *In vitro* enzyme-linked immunosorbent assay will be used to quantify the plasma of human BDNF (Table 1).

### Intervention

The intervention group will participate in online exercise program on two non-consecutive days per week for eight weeks via Tencent Conference Software. Each exercise session will include no more than eight participants. Participants will be guided and supervised by a professional coach during the entire online training. Each session will include a 10-min warm-up, a 25-min high-intensity or moderate-intensity interval training and a 10-min cool-down stretching. The training protocol is created by the first author who got fitness coach qualification certificate as well. Participants are expected to reach 70% of their age-predicted maximum heart rate (HR), which equals to 220 beats per minute-0.7 × age as an indicator of moderate intensity of aerobic exercise (59). Warm-up and cool-down exercises will include walking at low intensity (e.g., jogging in place) and stretching. Wearable devices (Huami amazfit neo smart bracelet) will be used during intervention to collect VO_2_ max.

Participants will be allowed to withdraw at any time during the trial. Some strategies will be used for adherence and compliance. For example, we will provide free follow-up service and online consulting service after program completion to encourage participants to complete the intervention. The smart bracelet will be sent to the participants for free. Completion of this program will be defined as finishing at least 50% of the exercise at each session and reaching at least 70% adherence rate of the whole intervention. The 70% adherence rate is defined as completing 11 sessions out of 16 sessions (Table 1).

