**Methods:**

This is a longitudinal, interventional, randomized, and single-blind trial. We plan to recruit 94 patients diagnosed with BD in depression episode. Patients will be randomly assigned to treatment as usual + aerobic exercise group (intervention group) and treatment as usual (TAU) only group, at a ratio of 1:1. The intervention group will undergo 40-min aerobic exercise training twice a week for eight weeks. The primary outcome of this study is the mean change of Hamilton Depression Rating Scale 17 (HAMD 17) scores from baseline to week 8. The Young Manic Rating Scale (YMRS), Self-Rating Depression Scale (SDS), and Interleukin-6 (IL-6), Tumor necrosis factor-α (TNF-α) and C-reactive protein (CRP) levels will also be measured. The measurements will be performed at baseline, immediately after intervention and two months after intervention.

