#### Inclusion criteria

1.Aged 18–50 years old, female or male.2.A diagnosis of BD depression episode according to the Diagnostic and Statistical Manual of Mental Disorders-5 (DSM-5).3.The score of HAMD ≥ 17, the score of YRMS < 6.4.Adequate audiovisual skills to complete the necessary checks for the study.5.Willing to participate in this trial, with signed written informed consent.

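### The heart-rate target is equated with a formula that cannot be 70% of maximum as written; the sentence supports two targets 55–62 bpm apart, and the intensity label and session length also disagree.

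*Protocol article*

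**What the plan says.** The Intervention section of the protocol article gives one heart-rate target: "Participants are expected to reach 70% of their age-predicted maximum heart rate (HR), which equals to 220 beats per minute-0.7 × age". It adds that this serves "as an indicator of moderate intensity of aerobic exercise".

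The same section describes each session as "a 10-min warm-up, a 25-min high-intensity or moderate-intensity interval training and a 10-min cool-down stretching". It gives no rule for when, or for whom, the main block is high rather than moderate intensity.

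The Methods paragraph of the abstract gives a different session length: "The intervention group will undergo 40-min aerobic exercise training twice a week for eight weeks".

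Three other statements bear on the point:

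- Eligible ages are fixed under Inclusion criteria: "Aged 18–50 years old, female or male".
- Sessions are supervised: "Participants will be guided and supervised by a professional coach during the entire online training".
- The Intervention section counts a participant as completing the programme if they finish half or more of the exercise in each session and meet an attendance threshold of 11 out of 16 sessions. The bracelets are said to collect VO2max; heart rate is not mentioned as something they record.

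**The concern.** The formula subtracts 0.7 times age from an unscaled 220. As a statement of 70% of maximum, that gives values far too high to be 70% of anything plausible, and it sits in the same sentence as a moderate-intensity label. As a statement of the maximum itself, it gives an ordinary-looking target after multiplying by 0.7. The grammar allows both readings.

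The first thing at stake is reproducibility. This is the only numerical intensity in the article, and the Discussion itself counts the way earlier trials defined intensity and duration among their limitations. A reader could not say from this text what intensity was prescribed.

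The second is safety, but only conditionally. It arises if someone applies the literal number as a working target. The participants are people who, under the Exclusion criteria, have exercised no more than 40 minutes a week over the last six months, and they train remotely in groups of up to eight.

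The session-length conflict matters less, but it changes what half of a session means in the completion rule. The per-protocol sensitivity analysis would naturally draw on that rule.

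**Working it through.** **Inputs from the article.** The 70% figure and the expression 220 − 0.7 × age (Intervention); ages 18 to 50 (Inclusion criteria); session parts of 10, 25 and 10 minutes and 16 sessions (Intervention); a 40-minute session (abstract, Methods).

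**Step 1. Literal reading: the expression is the 70% target.**

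- Age 18: 220 − 0.7 × 18 = 220 − 12.6 = 207.4 bpm.
- Age 50: 220 − 0.7 × 50 = 220 − 35 = 185.0 bpm.

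The maximum this implies is the target divided by 0.7:

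- Age 18: 207.4 / 0.7 = 296.3 bpm.
- Age 50: 185.0 / 0.7 = 264.3 bpm.

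Both exceed 220, the constant from which the article's own expression subtracts. The equality therefore cannot be reproduced, and showing this needs no outside formula.

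**Step 2. Alternative reading: the expression is the maximum.** The target is then 0.7 × (220 − 0.7 × age):

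- Age 18: 0.7 × 207.4 = 145.2 bpm.
- Age 50: 0.7 × 185.0 = 129.5 bpm.

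**Step 3. Distance between the two readings.**

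| Age | Literal target | Implied maximum | Target if the expression is the maximum | Gap |
|---|---|---|---|---|
| 18 | 207.4 | 296.3 | 145.2 | 62.2 |
| 30 | 199.0 | 284.3 | 139.3 | 59.7 |
| 40 | 192.0 | 274.3 | 134.4 | 57.6 |
| 50 | 185.0 | 264.3 | 129.5 | 55.5 |

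**Step 4. How hard is the literal target?** The article gives no separate maximum, so a yardstick has to be assumed. Taking 220 − age purely as an assumption (202 bpm at 18, 170 at 50), the literal target is 207.4 / 202 = 102.7% of maximum at 18 and 185 / 170 = 108.8% at 50. On the same assumption the alternative reading is 145.2 / 202 = 71.9% and 129.5 / 170 = 76.2%. Only the literal reading raises a safety question.

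**Step 5. Intensity label.** The main block is "a 25-min high-intensity or moderate-intensity interval training", while the only target is labelled moderate. The formula cannot settle which is meant, because its own reading is unresolved.

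**Step 6. Session length.** 10 + 25 + 10 = 45 minutes, against 40 in the abstract. Over 16 sessions that is 720 against 640 minutes. Half a session is 22.5 minutes on a 45-minute base, 20 on a 40-minute base, and 12.5 if only the 25-minute block counts as the exercise. On the 40-minute base, warm-up and cool-down alone (10 + 10 = 20 minutes) would reach the threshold.

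**The case against.** The strongest reply is grammatical. The words nearest to the equality are those naming the maximum heart rate, so the expression may define the maximum, and the moderate-intensity label may attach to reaching 70% of it. The target is then about 130–145 bpm and nothing is impossible. This reading is available and removes the safety concern. It does not settle the matter. The sentence can equally be read as equating the formula with the 70% target, the moderate label follows directly on the formula, and a maximum heart rate does not indicate moderate intensity. Nothing elsewhere in the article decides between them.

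A reader might infer that patients would be driven to maximal effort. The article does not support that. It mentions no bracelet alarm or heart-rate setting, a professional coach supervises every session, and whether anyone used the literal number cannot be known from this text.

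A reader might also infer that the intervention as a whole is undefined. It is not. Frequency, number of weeks and sessions, group size, online delivery, supervision and a completion rule are all stated. The article also refers to a training protocol that is not shown and may hold more session detail.

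Two further replies have some force. A level that participants are expected to reach could be a minimum, with harder work allowed above it, so the intensity wording may be ambiguous rather than contradictory. And a 5-minute difference in session length is small. Condensing a protocol into an article can explain missing detail, but it does not explain an equality that fails or two session lengths that disagree.

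**Conclusion.** The point holds as an error and ambiguity in the written intensity. Taken literally, the formula gives 207 to 185 bpm over ages 18 to 50 and implies a maximum of 296 to 264 bpm, so it cannot be 70% of maximum or a marker of moderate effort. Taken as the maximum, it gives a target of about 145 to 130 bpm. The sentence supports both, 55–62 bpm apart, and the article does not choose.

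These figures rest only on the article's own numbers. The comparison with maximal effort rests on the assumed yardstick of 220 − age, and any safety concern is conditional on the literal reading being applied despite coach supervision.

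The intensity label and the 45- versus 40-minute session are lesser conflicts. The session length matters mainly as the base of the completion rule. Randomisation, the HAMD-17 outcome and the sample size are not affected; what suffers is the description of the intervention being tested.

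**What to change.** The investigators should reconcile four items: the 70% figure, the formula, the high-or-moderate wording, and the session length. The result should be stated identically in the abstract, the Intervention section and the coach instructions, and should say plainly whether the formula denotes the maximum or the target. The completion rule should name the number of minutes to which its one-half refers. Which target, intensity and duration are intended is for the investigators to state.

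If the bracelets are confirmed to record heart rate (the article mentions only VO2max), achieved heart rate can be reported against the reconciled statement.

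The cost is protocol wording and a matching edit to the coach instructions. Reporting heart rate adds work only if that capture is confirmed.

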### Data collection methods

Two permanent research assistants, majoring in psychology with uniform training will perform all assessments at baseline and after eight weeks of intervention using standard procedure. Blood sampling for the analysis of biological parameters will be performed during the same visit.

## Anticipated results

We anticipate that the intervention group will benefit from the aerobic exercise at the end of intervention compared to the TAU group, with less severe depressive symptoms. The intervention may increase treatment compliance of patients as well. More evidence on exercise treatment for BD is needed to prove this hypothesis. In addition to the clinical outcome, we will also investigate whether exercise could improve the quality of life and physical fitness of patients.

## Dissemination

This protocol and the study results will be shared through publication in scientific journal, and national and international conferences.

## Discussion

This randomized controlled trial is designed to investigate whether exercise therapy is effective for patients with BD. To the best of our knowledge, this is the first randomized trial investigating the direct effect of aerobic exercise in patients with BD. This trial is expected to provide current evidence for adjunct exercise therapy for BD patients with depressive symptoms.

One of the most important aims of treatment is improving the clinical outcome of patients. The treatment of BD, especially treatment of depression episode in BD, remains a major challenge. Exercise as a psychosocial adjunct for BD should be assessed with rigorous randomized clinical trials.

Many studies have been conducted to certify that aerobic exercise should be used as an adjunct therapy for depression. However, a few randomized controlled trials have been conducted to investigate whether exercise treatment is useful for BD patients. As mentioned above, there is insufficient clinical trial evidence on exercise intervention for BD. The limitations of studies on exercise intervention among BD patients included small sample sizes, no distinction between different types of exercise (lifestyle physical activity or structured intervention program), definitions of the exercise intensity, duration, and frequency of exercise. Therefore, more high-quality evidence from randomized controlled trials are essential to investigate if exercise treatment is efficacious and safe for BD. If this trial can establish that exercise treatment is beneficial for clinical outcome of BD, people suffering from this illness may achieve better clinical outcome. Aerobic exercise can be easily performed, without any major adverse events. The results of this relatively small trial may be useful for the development of future exercise regimens for BD.

This trial also has some limitation. Firstly, it is not a large sample sized trial, and the recruitment may be difficult due to some reasons, such as the 8-week intervention duration, decreased motivation, busy schedule, sedentary habits. Additionally, this trial will be supervised by professional coach and psychotherapist, which may add bias during the trial. Also, the drop out of participants may be higher than expected. To address these problems, the researchers will keep in touch with participants and their doctors. Some inexpensive gifts and free physical examination will be provided to encourage participants to finish this intervention.

## Conclusion

This is a strictly designed randomized controlled trial aimed to provide high quality evidence for adjunct treatment of bipolar disorder. Our findings may provide additional evidence for better prognosis of patients with bipolar disorder. Larger sample should be included in future studies.

## Ethics statement

The studies involving human participants were reviewed and approved by Ethics Committee of the First Affiliated Hospital of Chongqing Medical University (March 23rd, 2022, Certificate No. 2022-065). The patients/participants provided their written informed consent to participate in this study.
